# A protocol for a cluster randomised feasibility study of an adolescent incentive intervention to increase uptake of HPV vaccination among girls

**DOI:** 10.1186/s40814-017-0126-y

**Published:** 2017-03-06

**Keywords:** Vaccination, Reward, Adolescent, Papillomavirus Vaccines, Motivation

## Abstract

**Background:**

Uptake of the human papillomavirus (HPV) vaccine in the UK is good, but there are pockets of the community who remain unprotected. Immunisation teams usually require written parental consent for a girl to receive the vaccine. Evidence suggests that uptake of the vaccine might be improved by promoting consent form return (if returned, forms are likely to grant consent). Incentivising girls to return consent forms is a promising approach to promoting consent form return. Before testing the efficacy of an incentive intervention in a randomised controlled trial (RCT), we must first establish whether the RCT is feasible. In this randomised feasibility study, we aim to establish the feasibility of conducting a cluster RCT of an adolescent incentive intervention to increase uptake of HPV vaccination.

**Methods:**

At least six schools will be randomised to either an incentive intervention arm or a standard invitation arm. Girls in standard invitation arm schools will receive the usual HPV vaccine programme invitation materials. Girls attending schools in the incentive intervention arm will receive the standard invitation and will also be told that they will receive an incentive if they return their consent form (regardless of whether consent is granted or denied). The incentive is being entered into a prize draw to win a retail voucher. Feasibility objectives include estimating the schools’ and parents’ willingness to participate in the study and be randomised; response rates to questionnaires; the extent of missing data; the girls’ and parents’ attitudes towards the incentive offered; school staff experiences of participating, fidelity to the trial procedures, data on any unintended consequences and the possible mechanisms of action, and proof-of-concept evidence of the effect of the intervention on consent form return rates and uptake of the vaccine. Analysis of feasibility outcomes will primarily be descriptive. Consent form return rates and uptake of the vaccine will be presented by trial arm without comparison.

**Discussion:**

Incentivising HPV vaccine consent form return may promote HPV vaccine uptake. This study will provide the evidence needed to establish whether testing this incentive intervention using a RCT design in the future is feasible.

**Trial registration:**

ISRCTN72136061

## Background

Human papillomavirus (HPV) is causally related to cancers of the cervix uteri, penis, vulva, vagina, anus and oropharynx. The development and worldwide implementation of vaccines against HPV has the potential to substantially reduce the burden of HPV-related cancers. A quadrivalent HPV vaccine is used in a UK HPV vaccination programme. This vaccine provides protection against HPV types 16 and 18 that are known to cause up to 80% of HPV-related cancers (depending on cancer site) [1, 2], as well as against HPV types 6 and 11 which cause most anogenital warts. Vaccination works best if administered to HPV-naïve individuals and in younger populations [3].

While uptake of the vaccine is high in England (89% of 12–13-year olds had at least one dose of the two-dose series in 2014/2015 [4]), there are pockets of the population who remain unvaccinated and there is huge variability in uptake between areas (from 68% in Kensington and Chelsea to over 99% in the Isle of Wight). Research exploring the association between socio-demographic characteristics and uptake of HPV vaccination has suggested that girls from some Black and Asian Minority Ethnic (BAME) backgrounds are less likely to receive HPV vaccination than girls from White British backgrounds [5, 6]. This remains the case when controlling for deprivation [7]. While high uptake in the UK should offer herd protection to those who remain unvaccinated, evidence of assortivity of sexual mixing exists [8, 9] (i.e. partnerships are more likely within ethnic groups than between them). As HPV is sexually transmitted, this may mean there are population subgroups who do not benefit from herd protection, thereby compounding disease inequalities. There is very little evidence about what might work in a UK setting to increase uptake of HPV vaccination [10, 11]. If an intervention is to be rolled out nationally, it will need to be simple and easy to implement given the increasing workload of immunisation teams (the child flu vaccine and a meningitis vaccine protecting against types A, C, W and Y vaccine have recently also be added to the immunisation schedule).

Informed consent is required for girls to receive the HPV vaccine. While girls themselves may consent to vaccination if they are deemed sufficiently competent, in practice immunisation, teams usually require written consent from their legal guardian [12]. In general, consent forms are sent home from school with the girl and are returned to the school in the same way. Consent forms must be returned regardless of the parent’s decision (granting consent to vaccinate or not). Unpublished data show that around 60% of consent forms are returned without prompting and of the remaining 40%, around half will consent to vaccination if followed up by a (time consuming) telephone call from an immunisation nurse [13]. This suggests that there is a group of parents who are open to providing consent, but who may not do so without prompting. Interventions aimed at promoting return of the consent form may, therefore, increase vaccination uptake. Incentives may be a promising approach, particularly as incentives work best for one-off behaviours [14–16], with the incentive being targeted at consent form return and not vaccination receipt. Various definitions of incentives have been used previously [17, 18] and often to suit the topic of interest. In the context of the present study, incentives will be defined as financial and non-financial rewards or penalties that may have a monetary or exchange value and are contingent on the target behaviour.

### Evidence for incentives in childhood immunisation

There is varying evidence from reviews about the use of financial incentives to increase uptake of immunisation. One systematic review [19] found that incentive interventions result only in a small increase in uptake, and another systematic review and meta-analysis reported that the evidence is not strong for their use in low- and middle-income countries [20]. A further systematic review found few studies that had examined effectiveness of incentives to increase uptake of preschool immunisations and only one had reported on the cost and consequences of such an intervention [21]. Contrarily, in a descriptive review of the literature, Sutherland et al [16] concluded that there is evidence that “modest incentives” increase uptake of vaccines and Dempsey et al. [22] argue that incentive interventions to increase vaccine uptake deserve further investigation. Models of optimising vaccination uptake have also recently been published that propose using incentives in this context (e.g. [23]). However, no trials have considered incentives provided contingent on vaccination consent form return^1^ and few studies have offered incentives to the child/adolescent rather than the parents or health professional. One experimental study found hepatitis B consent form return rates in Californian (USA) schools to be higher where classes were offered an incentive contingent on all consent forms being returned with 5 days of receipt [24] and as part of an Australian service evaluation, schools were offered the opportunity to receive an incentive if >90% of vaccination consent forms were returned [25]. However the results for incentives were not reported. In one UK trial, Mantzari et al. offered incentives to older adolescent girls (aged 17–18) to receive the HPV vaccine as part of a catch-up programme (delivered through GPs and pharmacies) [26]. The tested incentive comprised a total of £45 worth of Love2Shop retail vouchers, which are redeemable at over 20,000 UK shops: £20 for receiving doses one and three and £5 for receiving the second dose. The incentive increased uptake of the first and third doses. The offer of incentives did not affect the quality of the girls’ decision to get the vaccine, as measured by the congruence between their attitudes towards the vaccine and their vaccination status. A review of methods to increase postal questionnaire response rates found a two-fold improved response rate if monetary incentives were offered [27], although this was not necessarily among adolescents in a school-based setting.

### Mechanisms of action

Incentives in this context may work because they increase the perceived value of returning the consent form (congruent with expectancy value and economic models [28–33]). Incentives might also result in individuals allocating cognitive capacity to efforts to receive the incentive [34] or the immediate reward may enhance the short-term benefits of returning the consent form [35]. Incentives may also function as a way of focusing an individual’s attention to something that they had previously not considered [36, 37]. Among adolescents, there may also be a role of fear of missing out on something one’s peers are experiencing [38] and some evidence from neuroscience suggests that reward-related brain activation is linked to improved memory, implying that incentives make a behaviour more likely because the individual remembers it [39].

### Concerns about incentives

Use of incentives to improve health-related behaviours is generally acceptable to many stakeholders [40, 41], but varies depending on incentive type, its effectiveness, and the nature of the health behaviour being targeted [42]. Sociodemographic variation in attitudes to incentives has also been observed [17, 42], including ethnic variations, which are likely due to the acceptability of the behaviour the incentive is targeting, rather than the incentive itself [17]. Cash incentives are seen as less acceptable [41], and there is concern about the potential for abuse and fear of being part of a “Nanny State”. There is also concern about incentives undermining parental choice in immunisation decisions [26, 43]; alternatively, girls “pestering” their parents may encourage parents to engage with the decision.

We have conducted formative research with teachers and girls, as well as consulting our study user groups comprising parents and immunisation nurses, to choose an incentive that is acceptable to all vaccine stakeholders, as well as likely to be sufficiently motivational to girls. It will also be important to consider acceptability on a larger scale, as well as monitoring unintended consequences.

### The present study

It will be necessary to test the efficacy of the incentive intervention in increasing HPV vaccination uptake using a randomised controlled trial (RCT) design. Before this is appropriate, we must establish whether the RCT is feasible and establish parameters needed to design the RCT. The proposed study is a randomised feasibility study. Findings will inform the decision to conduct a future RCT and will provide proof-of-concept evidence.

It is not our intention that incentives should be offered to all girls as standard as part of the vaccination programme (should incentives be found effective at improving uptake), but that they be a tool that immunisation providers may use to improve uptake in schools with particularly low coverage.

### Aim

The aim of this study is to establish the feasibility of conducting a cluster RCT of an adolescent incentive intervention to increase uptake of HPV vaccination among girls.

### Objectives

Gain an estimate of school participation rates, parent participation rates, response rates to a parental questionnaire and response rates to girls’ questionnaire.Assess data quality and completeness.Determine the acceptability of the intervention and acceptability and fidelity of the trial procedures.Estimate the cost per returned consent form and cost per consent form that is agreeing to vaccination.Identify longer term cost components that need to be considered in a future economic evaluation.Obtain data on unintended consequences of the intervention and mechanisms of action.Generate proof-of-concept evidence of the effect of the intervention on HPV vaccination uptake.Generate proof-of-concept evidence of the effect of the intervention on consent form return rates.

## Methods/design

### Trial design

The trial design is a two-arm cluster randomised feasibility trial, with equal allocation to each arm (see Fig. 1).

**Fig. 1 Fig1:**
[figure not shown]
Trial flow diagram

### Setting

The study will be conducted in the London boroughs of Enfield, Lambeth and Southwark. In Enfield, uptake of dose one of the two-dose HPV vaccine schedule is 75% (the fourth lowest in the country; [4]) and around 49% of residents are from a non-White British ethnic background (predominantly other White^2^ and Black or Black British Caribbean; [44]). Uptake of dose one in Lambeth is 82% (average for London, but below average for England; [4]) and 60% of residents are from a non-White British ethnic background, mainly Black African and Black Caribbean [45]. Southwark has a similar dose one uptake rate to Lambeth (83%; [4]) and around 42% of residents are from a non-White background, again, mainly Black African or Black Caribbean [46].

### Eligibility criteria

Secondary schools participating in the HPV immunisation programme in Enfield, Lambeth or Southwark are eligible for the study. Within participating schools, adolescent girls in school year eight are eligible to take part. Feasibility data will also be collected from one parent of each participating girl, school staff working in participating schools and HPV-related cancer prevention stakeholders. There are no exclusion criteria.

### Interventions

The feasibility trial has two arms: (1) standard invitation and (2) incentive intervention plus standard invitation. The standard invitation arm comprises adolescents being provided with an information leaflet about the HPV vaccine and a consent form by their school, which they are asked to give to their parents (delivered by hand) and return to the school before a prescribed date. Immunisation nurses may engage in additional promotional activities with schools, and this information will be collected. Participants in the incentive intervention arm will receive the standard invitation. They will also be advised by their school form tutor and in a letter that they will be entered into a prize draw to win a £50 “Love2Shop” voucher if they return their consent form, with a 1 in 10 chances of winning. It will be made clear that they will be eligible for the incentive regardless of whether consent is given. Schools in the intervention arm will be asked to record the day the students are informed about the incentive and the name of the teacher who did this.

The incentive aims to improve uptake among the 20% of the eligible population who will consent to vaccination if prompted to return their consent form; however, for practical purposes, all girls in the intervention arm will be eligible to receive the incentive if their consent form is returned.

### Outcomes

Feasibility outcomes collected prior to interventions being administered include the schools’ and parents’ willingness to participate in the study and the schools’ willingness to be randomised (number of schools contacted, number of those who express initial interest, and number of those who participate). Feasibility outcomes collected following interventions being administered include response rates to questionnaires by the parents and girls and data completeness regarding the proportion of missing data, girls’ and parents’ socio-demographic characteristics (including ethnicity, ascertained through brief questionnaires, and index of multiple deprivation (IMD) score, ascertained using the girls’ postcodes provided by the schools). We will also explore the girls’ and parents’ attitudes towards the incentive offered (assessed through brief questionnaires, measure developed for this study) and school staff experiences of participating (ascertained through brief interviews). Data on unintended consequences and mechanisms of effect will be collected via questionnaires. Unintended consequences include the girls’ perceptions of why an incentive was offered, the girls’ attitudes towards returning future consent forms (measures developed for this study) and whether parents made an informed decision about vaccination (using questions described in [26]). Mechanisms of effect include whether the incentive increased motivation for returning the consent form, improved memory for returning the form, increased salience for returning the form, increased the short-term benefits of returning the form, increased the perceived value of returning the form and whether there is a role for girls fearing missing out on the incentive (using [38] and measures developed for this study). Trial procedures will be documented by speaking to the school staff about their fidelity to the intervention (ascertained through brief interviews) and taking a detailed description of immunisation processes performed in each school (i.e. what additions to the standard invitation were performed) by the immunisation teams and school staff (ascertained through brief interviews with school staff and email/telephone conversations with immunisation teams throughout the trial). Cost of the incentive intervention will be assessed by measuring (1) the cost per returned consent form and (2) the cost per form consenting to vaccination.

Proof of concept outcomes collected following the first vaccination dose, including initiation of the vaccination series, will be assessed by collecting data on whether consent was given to vaccination reported by schools and self-reported by parents in a brief questionnaire (measure developed for this study). Consent form return rates will be based on information collected by schools.

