### Study procedures

All secondary schools in Enfield, Lambeth and Southwark will be approached. Legal guardians (usually parents) from participating schools will be written to/emailed explaining the study and those not wishing to participate were asked to opt out to a school contact.

Schools randomised to the incentive intervention arm will be sent the intervention letter to give to students and teachers informed to tell students that they will be eligible for the incentive if their consent form is returned. At the same time, parents from schools in both arms will be asked by the immunisation team to consent to their daughter having the HPV vaccine as part of the routine programme, via an invitation letter, information leaflet and accompanying consent form. These standard immunisation programme materials are distributed to the girls by form tutors and their distribution/content is unaffected by the present study.

Following dose one of the vaccine being administered to those girls with consent, the research team will give the school administrative staff a list of unique anonymised identifiers to assign to each participating girl. The administrative team will add this list to an existing dataset containing all vaccine-eligible girls and the following information: an IMD score for each girl (derived from the girls’ postcodes), whether she returned a consent form and whether consent to vaccination was given on the consent form. Administrative staff will remove the girls’ names from the dataset and provide this to the researchers to take away from the school site.

Girls will be given a questionnaire to complete in the week after vaccination day by their form tutor, as well as a questionnaire pack to hand deliver to their parents. The parents’ packs will include a FREEPOST return envelope to send the questionnaires directly to researchers. Both questionnaires will be labelled with each girl’s unique identifier. Parents with more than one daughter in year eight will be asked to think of one child and respond about that child when completing the questionnaire. Girls will complete the questionnaire during a tutor group session. School staff will be invited to participate in a brief interview in an email sent from the research team via a member of the school administrative staff.

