### Statistical methods

As this is a feasibility study our primary focus will be on assessing the outcomes regarding trial procedures, data quality and estimates of design parameters. The analysis for the feasibility outcomes will be primarily descriptive. School characteristics will be presented by arm. Data are available on participating and non-participating schools regarding school size, whether schools are single sex/mixed, and HPV vaccine uptake in the previous year. Participating and non-participating schools will be compared descriptively based on these factors to examine how representative participating schools are of their respective boroughs. Participant characteristics at baseline will be presented overall, by arm and by school. We will estimate and report on the proportion of schools approached that participate, the proportion of parents approached who opt out of the study, the proportion of parents sent a questionnaire who return the questionnaire and the proportion of girls given a questionnaire who complete the questionnaire.

We will estimate and report on the proportion of missing data for consent form return rates, vaccination consent, girls’ IMD score and all questionnaire items.

Acceptability of the incentive among girls and parents will be assessed descriptively. Interviews will be analysed descriptively to assess the range of opinions.

Parents’ mean informed decision-making scores will be presented by cluster and by trial arm, as will the data for other unintended consequences and mechanisms of action. We will summarise by cluster and by trial arm, the proportion of girls whose parents consent to the vaccine and the proportion of consent forms returned.

The trial will be reported according to the CONSORT extension to cluster randomised trials, CONSORT extension to randomised pilot and feasibility trials and this protocol has been prepared using the SPIRIT guideline [47–49].

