## Discussion

We have presented a protocol for a cluster randomised feasibility study of an adolescent incentive intervention to increase uptake of HPV vaccination among girls. The study will help provide the answers to questions required to design any main trial and whether it is appropriate to proceed with a future trial.

We have previously achieved high response rates to questionnaires completed by students in schools; however, response rates to questionnaires posted to parents are likely to be lower. Findings from this study will determine whether this approach to data collection from parents is likely to be successful in any main trial. We will also be able to observe if certain questionnaire items are often missing, suggesting that participants either did not understand them or did not find them relevant, allowing us to modify the questionnaires prior to any main trial. Interviews with school staff may also help to explain any missing data. Finally, we presently do not know if we will obtain more complete data on vaccination status by asking schools to record this data or by asking parents to report their daughter’s vaccination status. Findings of this feasibility study will suggest how best to collect data on vaccination status in any main trial.

The sample size is based on a conservative scenario and if achieved will allow us to estimate binary feasibility outcomes. For any main trial, a larger sample size will likely be required; this will be determined following this feasibility study. It is possible that schools participating in the feasibility study will be the most engaged in research. Further efforts may be required to recruit additional schools for any main trial and may require input from senior leadership to facilitate recruitment, such as local authorities. We have engaged with local authorities in the set-up of this feasibility study, so their input should be possible in any main trial.

Uptake of the HPV vaccine among eligible 12–13-year-old girls is sub-optimal in some populations. An incentive intervention to promote consent form return may result in improved uptake. This cluster randomised feasibility study will provide the evidence needed to decide if a future RCT testing the efficacy of such an intervention is feasible.

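### Vaccine uptake is an objective and a by-arm output, but the outcome definition, school data fields and summaries cover only consent and form return

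*Protocol article*

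**What the plan says.** Three places in the protocol article speak of vaccination itself:

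- Objectives: "Generate proof-of-concept evidence of the effect of the intervention on HPV vaccination uptake". This is listed separately from the objective on form return.
- Abstract, Methods: "Consent form return rates and uptake of the vaccine will be presented by trial arm without comparison".
- Discussion: "Findings of this feasibility study will suggest how best to collect data on vaccination status in any main trial".

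Three operational sections speak of consent:

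- Outcomes says that the proof-of-concept measures, "including initiation of the vaccination series, will be assessed by collecting data on whether consent was given to vaccination reported by schools", with parents self-reporting in a questionnaire as the second source.
- Study procedures lists the school dataset: a deprivation score, then "whether she returned a consent form and whether consent to vaccination was given on the consent form". It is drawn up at this point: "Following dose one of the vaccine being administered to those girls with consent".
- Statistical methods summarises, by cluster and by arm, "the proportion of girls whose parents consent to the vaccine and the proportion of consent forms returned". The missing-data list in the same section names form return, vaccination consent, deprivation score and questionnaire items. It does not name vaccination.

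**The concern.** Consent and receipt of dose one are different events, and they can disagree in both directions. A girl whose parent consented may be absent, unwell or unwilling on the day. A girl vaccinated after a telephone call, or on her own consent, may have no consent recorded on a form. Background mentions both of these routes.

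Two outputs are at stake. The first is the uptake evidence, which would be consent data under another name. The second is the advice on how to collect vaccination status in a main trial. Comparing two sources of consent data cannot show which source captures vaccination better.

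The second kind of disagreement might also fall unequally on the arms. The incentive acts on return of the form, and Background says of parents who do not return it unprompted that "around half will consent to vaccination if followed up by a (time consuming) telephone call from an immunisation nurse". Those families are the group that the incentive is meant to move.

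**Working it through.** **Step 1. Trace uptake through the article.**

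| Stage | Section | What is specified |
|---|---|---|
| Aim | Objectives | Effect on uptake |
| Promised output | Abstract, Methods | Uptake by arm, no comparison |
| Outcome definition | Outcomes | Series initiation, assessed through consent |
| School data | Study procedures | Deprivation score, form returned, consent on form |
| Summary | Statistical methods | Proportion consenting, proportion of forms returned |
| Promised lesson | Discussion | How to collect vaccination status |

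The first two rows and the last concern vaccination. The three between them concern consent. No dose-received item appears, although the school dataset is prepared after dose one has been given. This step needs no assumption.

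**Step 2. Reproduce the protocol's 20%.** Background gives about 60% of forms returned unprompted and, of the other 40%, about half consenting after a call: 0.40 × 0.5 = 0.20. Interventions gives the same 20% as the incentive's target group.

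**Step 3. Possible distortion from telephone consent.** Suppose that every consenting girl is vaccinated, and that the whole 20% is reached in both arms, by form or by telephone. True uptake is then equal in both arms. Three quantities are not in the article and are assumptions:

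- g: share of unprompted forms that grant consent
- f: share of the 20% who return a form because of the incentive
- q: share of telephone consents entered as consent on the form

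Then:

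- True uptake, both arms: 0.6g + 0.2 (80% if g = 1)
- Consent on form, standard arm: 0.6g + 0.2q
- Consent on form, incentive arm: 0.6g + 0.2f + 0.2(1 − f)q
- Apparent difference: 0.2f(1 − q), whatever the value of g

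| | f = 0.25 | f = 0.5 | f = 1 |
|---|---|---|---|
| q = 0 | 5 points | 10 points | 20 points |
| q = 0.5 | 2.5 points | 5 points | 10 points |
| q = 1 | 0 | 0 | 0 |

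In the standard arm alone, the understatement is 0.2(1 − q), which is 0 to 20 points.

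**Step 4. Consent without a dose.** The article gives no rate. If a share d of consented girls misses dose one, consent overstates uptake by d times the consent rate. With 80% consent and an assumed d of 2% to 5%, that is 0.80 × 0.02 = 1.6 points to 0.80 × 0.05 = 4.0 points. This only shows scale; the finding does not depend on it.

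**The case against.** The strongest reply has four parts.

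**Vaccination status may be collected after all.** The Discussion weighs schools recording it against parents reporting it. The parent questionnaire was developed for this study and is not shown, and a journal article condenses the full protocol. A reader might infer from Step 1 that the study never measures uptake. The documents do not support that. They show that the Discussion disagrees with Outcomes, Study procedures and Statistical methods, and that no dose item is specified. This part of the reply stands. It does not remove the finding, because the article does define the outcome, the fields and the summaries, and defines them as consent.

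**The arm-differential distortion is not demonstrated.** Background says teams usually want the legal guardian's consent in writing. Interventions describes the 20% as families who consent once prompted to return the form. The dataset is drawn up late enough to count late forms. All this leans towards q near 1, where the distortion is zero. No passage says that standard-arm families are called more often. The plan will also record additional promotional activity by immunisation teams, but at school level, which cannot correct an individual girl's status. A reader might infer that the by-arm figures are biased; the documents support only that they could be. The 20-point maximum needs two extremes together, and the 60% and one-half are approximate unpublished figures.

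**No decision turns on an uptake difference.** The abstract rules out a comparison, and the section on proceeding to a full trial relies on acceptability, feasibility and scalability. This stands, and it limits the harm.

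**The proxy is declared, and the Discussion asks about completeness.** Outcomes says how initiation is assessed, Statistical methods labels its summary as consent, and missingness of the consent data will be reported. So completeness by source is partly covered, but for consent and not for vaccination.

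**Conclusion.** The inconsistency holds without any assumption: uptake is promised, and what is defined, listed and summarised is consent and form return. Followed as written, the plan would present consent under the name uptake and would have no specified data behind its advice on vaccination status.

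The numerical effect is unknown. The difference between arms could be distorted by 0 points if every telephone consent is entered as consent on the form, and by at most 20 points in theory if none is and the incentive moves the whole target group. The non-attendance gap cannot be sized from the article.

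With no between-arm comparison and no uptake-based progression rule, the consequence is mislabelled proof-of-concept data and unsupported guidance for the main trial. It is not a biased test and does not undermine the feasibility outcomes. The point is worth correcting because the repair is small and concerns a stated objective, but it is not a fatal flaw.

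**What to change.** **Preferred.** Add one field to the school dataset in Study procedures: *dose one received on or before the extract date (yes/no)*, taken from the immunisation team's session record. Define uptake on that field and report it separately from *consent to vaccination*. State how consent given by telephone is coded.

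**Cost.** One extra column. School staff must match the session record to each girl before names are removed, so that no identifiable data leave the school. Recruitment ended on 15 December 2016, so the dataset may already exist. Adding the field afterwards would need the school still to be able to link identifiers to girls, which the article does not address.

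**If the field cannot be obtained.** Replace *uptake* (and, under Outcomes, series initiation) with *consent to vaccination* in the abstract, Objectives and Outcomes. Limit the Discussion's claim to how complete the consent data are from each source. This costs only wording.
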